### Economic analysis

In addition to analyses of clinical effectiveness, we will assess the cost-effectiveness of the interventions in the two staff groups from a healthcare and societal perspective. Healthcare costs will be calculated for the 12-month follow-up period and will be based on the number of contacts with clinical staff (occupational health, primary care staff, dermatologists, etc.) as a result of hand dermatitis, combined with appropriate unit cost information [40] and the cost of supplying moisturising creams (with costs obtained from the *British National Formulary* (*BNF*) for prescribed formulations). The service use information will be collected using a short self-report schedule based on the Client Service Receipt Inventory. These service costs will be added to the cost of the BCP itself, which will be based on development time and staff time accessing the package. Societal costs will be calculated by adding healthcare costs to the costs of lost production, based on days off work combined with wage rates. Cost comparisons between the groups will be made using bootstrapped regression models assuming that the cost data are skewed. Costs from both perspectives will be combined with the primary outcome measure in a cost-effectiveness analysis. If costs are reduced for one group and outcomes are better then it will be ‘dominant’. If one group has higher costs and better outcomes then incremental cost-effectiveness ratios (ICERs) will be generated, defined as the difference in costs divided by the difference in outcomes. Using the primary outcome measure, the ICER will indicate the extra cost incurred for one extra participant to be free of visible hand dermatitis in either hand at 12-month follow-up. There will be uncertainty around the cost and effectiveness estimates and this will be addressed using cost-effectiveness planes generated through repeated resampling from the data set to generate 1000 cost-outcome combinations and plotting these. To inform healthcare spending decisions it is helpful also to combine costs with quality-adjusted life years (QALYs). The most widely used QALY measure in England is the EQ-5D, which has been recommended for dermatological interventions [36]. This measure will be used at baseline and follow-up, and area under the curve methods used to produce QALYs. Similar analyses to those described above will be conducted to assess the relationship between costs and QALYs, but we will also generate cost-effectiveness acceptability curves (CEACs) to show the probability that the intervention is cost-effective for different threshold values placed on a QALY [41]. CEACs will still be produced but will be more exploratory; they will be used to identify threshold values where the likelihood of the intervention being cost-effective is 50 %, 60 %, 70 %, 80 % and 90 %). While standard unit costs are being used for most services it will be necessary to calculate the intervention costs specifically for the study. This will be based on estimates of staff time spent developing the intervention and staff time spent accessing it. We will increase/decrease both of these aspects in sensitivity analyses by 10–50 % to see the impact that these changes have on the probability that the intervention is cost-effective at the £20,000 and £30,000 QALY thresholds. Sensitivity analyses will also be conducted on the societal cost-effectiveness estimates by increasing/decreasing the cost of lost work time by 10–50 % and assessing the impact on the CEACs.

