
If the intervention is shown to be cost-effective then we will make estimates of the number of nurses who might access the intervention were it to become recommended practice. This will in turn allow us to estimate the budget impact for the NHS and the benefits in terms of total QALYs gained. Uncertainty around these estimates will be investigated through the sensitivity analyses describe above.

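### The sensitivity analyses named for the NHS projection vary only costs, so as written total QALYs get no range and the budget impact only a partial one

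*Protocol article*

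**What the plan says.** All of this is in the Economic analysis section of the protocol article.

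- **The projection.** If cost-effectiveness is shown, "we will make estimates of the number of nurses who might access the intervention were it to become recommended practice". Then: "This will in turn allow us to estimate the budget impact for the NHS and the benefits in terms of total QALYs gained".
- **Its uncertainty.** "Uncertainty around these estimates will be investigated through the sensitivity analyses describe above". No other tool is named for the two totals.
- **First sensitivity analysis.** It concerns the cost of the intervention: "This will be based on estimates of staff time spent developing the intervention and staff time spent accessing it". The variation is stated next: "We will increase/decrease both of these aspects in sensitivity analyses by 10–50 % to see the impact". The result is read as the chance of cost-effectiveness at £20,000 and £30,000 per QALY.
- **Second sensitivity analysis.** "Sensitivity analyses will also be conducted on the societal cost-effectiveness estimates by increasing/decreasing the cost of lost work time", again by 10–50 %, read through the acceptability curves.
- **Sampling error.** This is treated separately, with cost-effectiveness planes from "repeated resampling from the data set to generate 1000 cost-outcome combinations". Similar analyses are promised for QALYs.
- **Source of the QALYs.** EQ-5D at baseline and follow-up, by area under the curve.

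**The concern.** The closing paragraph fixes a method for exploring uncertainty in two outputs, and for one of them that method cannot work. A national QALY total is the number of nurses times the gain per nurse. Changing what the package costs, or what a lost day costs, alters neither factor. Followed literally, the plan would present an estimated gain as a fixed national benefit and describe it as having been through sensitivity analysis.

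The budget impact would show a range, but only for the cost of building and using the BCP. The number of nurses, which multiplies the per-nurse figures in both totals, would have no stated range. These totals are the output addressed most directly to NHS adoption. They are also produced only after a favourable result, when a point figure without an interval is more likely to flatter.

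**Working it through.** The article states no budget-impact or QALY figure, so there is nothing to reproduce. The check is structural, followed by an illustration of scale.

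**1. Structure.** With N nurses:

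- Total QALYs = N × QALY gain per nurse.
- NHS budget impact = development cost + N × (access cost + cream and service cost).
- Societal total = budget impact − N × value of lost work avoided.

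This assumes that the budget impact is built from the section's healthcare costs. The section adds lost production only when it moves to the societal view.

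**2. Apply the stated variations.** The inputs are placeholders, chosen only to see what moves: N = 100,000; gain 0.002; development 100,000; access 10; services 5; lost work 8.

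Base case:
- QALYs = 100,000 × 0.002 = 200.
- Budget = 100,000 + 100,000 × (10 + 5) = 1,600,000.
- Societal total = 1,600,000 − 100,000 × 8 = 800,000.

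| Input changed by ±50 % | Total QALYs | NHS budget impact | Societal total |
|---|---|---|---|
| Development time | 200 | 1,550,000 to 1,650,000 | 750,000 to 850,000 |
| Access time | 200 | 1,100,000 to 2,100,000 | 300,000 to 1,300,000 |
| Cost of lost work | 200 | 1,600,000 (unchanged) | 400,000 to 1,200,000 |

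Changes of ±10 % show the same pattern. The QALY total was unchanged in all 12 runs (three inputs, four changes each). This does not depend on the placeholder values, because none of the three inputs appears in the QALY formula.

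**3. Illustration of what is left out.** The 95 % half-width of the QALY difference per nurse is 1.96 × SD × √(2 × VIF / n per arm), where VIF is the variance inflation factor.

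The Sample size section gives an intraclass correlation of 0.05 and VIFs of 2.05 (students) and 2.8 (ICU). The implied cluster sizes are 1 + 1.05/0.05 = 22 and 1 + 1.80/0.05 = 37. The site counts are 12 + 5 = 17 and 12 + 18 = 30. Hence n per arm is 22 × 17/2 = 187 and 37 × 30/2 = 555.

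The QALY SD is not in the article; 0.05 to 0.20 is assumed. Applying the article's intraclass correlation for dermatitis to QALYs is also an assumption.

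- Students, SD 0.05: 1.96 × 0.05 × √(4.10/187) = 0.0145. SD 0.20: 0.058.
- ICU, SD 0.05: 1.96 × 0.05 × √(5.60/555) = 0.0098. SD 0.20: 0.039.

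Per 1000 nurses that is about ±14.5 to ±58 QALYs for students and ±10 to ±39 for ICU nurses, before any uncertainty in the number of nurses.

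**The case against.** **The cross-reference may be meant to include the resampling.** Both sensitivity analyses are read through cost-effectiveness probabilities or acceptability curves, which naturally rest on the resampled cost–QALY pairs. A range of zero follows only if the cost changes are applied to point estimates. This has some force, since the authors may intend the resamples to feed the totals. But the section introduces the resampling separately, does not call it a sensitivity analysis, and does not mention it again for the projection. Even on this reading the number of nurses is not varied.

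**An article leaves detail to the full plan.** This stands for how the number of nurses will be ranged. A reader might infer that one fixed number is intended, but the text does not say so. It does not excuse the cross-reference, which commits to a particular method.

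**The site-exclusion analysis under Method of analysis could shift the QALY gain.** It is conditional on confounding changes at sites, belongs to the clinical outcomes, and addresses neither sampling error nor uptake.

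Three stronger readings are tempting and are not supported:

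- *QALY uncertainty is ignored throughout.* It is not; the resampling deals with it at trial level.
- *Neither total gets a range.* The budget impact gets one from the two BCP inputs.
- *The omitted uncertainty exceeds the gain by some stated multiple.* Any such ratio needs a QALY SD and a utility loss per case of dermatitis, and the article gives neither.

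**Conclusion.** The point holds. The analyses named for uncertainty in the national totals are all changes to cost inputs. As written they give no range for total QALYs and a partial one for the NHS budget impact. The QALY result follows from the definitions and needs no numerical assumption. The statement that lost work time leaves the budget impact unchanged rests on that impact being built from healthcare costs as the section defines them.

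The gap is that a planned trial-level distribution is not carried forward and that no range is stated for the number of nurses. The half-widths above are illustrative only, because they rest on an assumed QALY SD. Severity is minor: the projection is secondary, is made only after a finding of cost-effectiveness, and touches no clinical outcome or primary analysis.

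**What to change.** Replace the last sentence of the Economic analysis section with wording such as:

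*Each resampled cost–QALY pair from the trial analysis, drawn so as to respect clustering by site, will be multiplied by the projected number of nurses, separately for student and ICU nurses, to give 95 % intervals for budget impact and total QALYs. The projected number of nurses will be varied over a stated plausible range, informed by but not limited to uptake in the trial. The 10–50 % cost analyses will be shown in addition.*

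Two details matter. The article does not say that the resampling respects sites, and without that the intervals would tend to be too narrow. Trial uptake is obtained with field-worker promotion and study reminders, so it can inform the range for national rollout but should not set its limits.

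The cost is a short change of wording and a few lines of code on resamples already planned; BCP access and completion are already collected under Process evaluation. The national figure will look less certain.

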#### Process evaluation

We will collect data on and describe:Uptake of the intervention, in terms of:Proportion of eligible nurses who access the online BCPProportion of eligible nurses who complete the online BCPAcceptability of the intervention in terms of:Perceived interest, relevance to role and likelihood of recommending it to colleagues

## Discussion

A range of operational and practical issues have arisen during the planning and implementation of the trial, including:A large number of sites whose personnel had initially expressed an interest in taking part in the study were later unable to proceed due to various local issues (e.g. a subsequent reduction in OH staff to support the study or an increase in routine operational workload). As a consequence, it was necessary to invite additional OH services to take part in the study. This has enabled the research team to increase the total number of sites taking part in the study from the number initially plannedThe recruitment rate in some sites has been lower than expected; therefore, to improve the number of participants taking part in the study, the research team have requested participating sites (where possible) to undertake a second round of recruitment. In addition, the research team agree to broaden the inclusion criteria for ‘critical care nurses’ to also include ‘special care baby unit’ nurses:A dedicated full-time research nurse has been recruited to the central research. Their role will be to assist with further recruitment and capturing follow-up data at participating sites

### Trial status

At the time of submission, the main trial has been underway since September 2014, with final recruitment planned for March 2016. The trial will be completed no later than September 2017 (pending approval from the funder).

## Abbreviations

BCP: behavioural change programme
CEACs: cost-effectiveness acceptability curves
CONSORT: Consolidated Standards of Reporting Trials
CTU: Clinical Trials Unit
EQ-5D: EuroQol-5D
HSE: Health and Safety Executive
HTA: Health Technology Assessment
ICERs: incremental cost-effectiveness ratios
ICU: intensive care units
MRC: Medical Research Council
MRSA: methicillin-resistant *Staphylococcus aureus*
NHS: National Health Service
NICE: National Institute for Health and Clinical Excellence
NIHR: National Institute for Health Research
OH: occupational health
QALYs: quality-adjusted life years
RCN: Royal College of Nursing
RCT: randomised controlled trial
TEWL: transepidermal water loss
TPB: Theory of Planned Behaviour
UKCRC: UK Clinical Research Collaboration
WHO: World Health Organization
